#### Economic evaluation measures

The following will be evaluated for the economic impact of the C-spine rule: radiography rates after discharge will be determined by a random sample of 5% of "after" phase patients, who will be followed by telephone interview 30 days after the initial ED visit. This will ascertain if the patient has obtained cervical spine radiography through a family physician, clinic, or ED. We also will examine the length of stay in the ED (in hospital), if admitted, hospital admission for CSI (as opposed to other injuries), and operative repair of CSI.

### Data analysis

#### Measures of clinical impact

Every eligible patient who satisfies the inclusion and exclusion criteria during each of the three periods at all 12 sites will be included in the final analysis. No patient will be excluded due to non-compliance by the physicians or radiology departments. Sub-group analyses will evaluate teaching and community hospitals separately. Comparison of patient characteristics will be tested. All *p *values will be two-tailed. The primary analyses will compare the "before" and "after" periods. Secondary analyses will compare the "after" and "decay" periods in order to evaluate sustainability.

For the analysis of dichotomous data from this matched-pair design, a parametric approach will be used, based on the standard paired t-test (with *k*-1 = 5 degrees of freedom) to the differences in the event rates in the intervention and control site pairs. Although the assumptions of equal variances and approximate normality may not be satisfied, empirical studies suggest that this test procedure is robust to departures from these assumptions [52-54]. It is expected that the cluster sizes will be similar, but if they are highly variable, then a weighted t-test after transformation of the event rates to the logistic scale will be considered, as suggested by Donner and Donald [53]. Given the small number of pairs, exact procedures based on permutation tests also will be considered. Further, 95% confidence intervals will be calculated for the relative reductions in event rates. Similarly for the analysis of continuous data, the standard paired t-test (with *k*-1 = 5 degrees of freedom) to the differences in the mean response between the intervention and control site pairs will be used. If the relevant information from the previous period is available, the change from baseline for each cluster will be determined and used in the calculation of the difference in the event rate or response for each intervention and control site pair.

For each of the following clinical impact outcome variables, the change from the "before" to "after" periods in the proportions (or means) for each cluster will be determined, used in the calculation of the differences in the event rates (mean response) for each intervention and control site pair, and analyzed according to the above analysis plan. Clinical impact outcome variables include: cervical spine radiography ordering proportions, proportion of missed fractures, proportion of serious adverse outcomes, length of stay in ED in minutes and, patient satisfaction with the proportions indicating "very satisfied" or "satisfied."

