#### Specific objectives

The goal of phase III is to evaluate the effectiveness and safety of an active strategy to implement the Canadian C-Spine Rule into physician practice in multiple EDs, compared to a control strategy that relies upon passive measures. Specific objectives are to:

*Determine clinical impact *by comparing the intervention and control sites, individually and collectively, during the "before" and "after" periods for:

a) Cervical spine radiography rates, such as proportion of potential injury patients referred for radiography; this is the primary study objective;

b) Number of missed CSI, such as clinically important CSI not identified during initial ED visit;

c) Number of serious adverse outcomes, such as development of neurological deficit after initial assessment in ED;

d) Length of stay in the ED, such as the time from arrival until discharge; and

e) Patient satisfaction with ED care, particularly when cervical spine radiography is not ordered.

*Determine sustainability *of clinical impact by comparing the intervention and control sites, individually and collectively, during the "after" and "decay" periods for objectives a)-d) above.

*Evaluate performance *of the Canadian C-Spine Rule, during the "after" period at the intervention sites:

a) Accuracy of the rule, such as sensitivity and specificity for identifying clinically important CSI;

b) Physician accuracy in interpretation of the rule; and

c) Physician comfort and compliance with use.

*Conduct an economic evaluation *to determine the potential for cost savings with widespread implementation of the rule.

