## Methods

### Design

We propose to conduct a matched-pair cluster design study that compares outcome measures during three consecutive 12-month "before," "after," and "decay" periods at six pairs of "intervention" and "control" sites (Figure 3) [45]. These 12 hospital ED sites will be stratified by the classification of "teaching" or "community" hospital, and matched according to baseline cervical spine radiography ordering rates during the "before" periods. Using computer-generated numbers, sites within each pair will be randomly allocated to either intervention or control groups by our senior biostatistician. During the "after" period at the control sites, there will be no specific implementation strategies, and physicians will order radiography according to personal judgment. During the "after" period at the intervention sites, strategies will be employed to actively implement the Canadian C-Spine Rule into physician practice. This "after" period will evaluate the time to full effect, as well as maximum effect of the implementation. During the third 12-month period – the "decay" period – implementation strategies will continue as in the "after" period. This will allow us to evaluate the sustainability of the effect of implementation, such as whether our simple and inexpensive implementation strategy can be expected to have a long-term effect, or whether there will be significant decay. Due to the nature of this intervention, blinding will not be possible.

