#### Sustainability of the intervention

The same clinical impact measures will be collected during the "decay" period to determine whether the effects achieved during the "after" period have been sustained.

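### For missed injuries and serious adverse outcomes, no named analysis combines the two years under the rule, and an after-to-decay change score cannot show a constant harm

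*Protocol article*

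**What the plan says.** Under Data analysis, Measures of clinical impact, the protocol states that "The primary analyses will compare the 'before' and 'after' periods" and that "Secondary analyses will compare the 'after' and 'decay' periods in order to evaluate sustainability". The basic test is a paired t-test with 5 degrees of freedom on the "differences in the event rates in the intervention and control site pairs". For the clinical impact outcomes, which include missed fractures and serious adverse outcomes, "the change from the 'before' to 'after' periods in the proportions (or means) for each cluster will be determined" and then compared within pairs. No equivalent change score is written out for 'decay'. A more general sentence in the same section reads "If the relevant information from the previous period is available, the change from baseline for each cluster will be determined".

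Specific objectives gives evaluation of both effectiveness and safety as the goal. It extends the sustainability comparison of intervention and control sites to harms with the words "during the 'after' and 'decay' periods for objectives a)-d) above"; items b) and c) are missed injuries and serious adverse outcomes. Sustainability of the intervention confirms that "The same clinical impact measures will be collected during the 'decay' period". Design says that in the third year "implementation strategies will continue as in the 'after' period".

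**The concern.** A before/after then after/decay structure suits the radiography rate, where the second-year question is whether the effect fades. For rare harms the question is different: are patients managed under the rule safe, over all the time it is in use? In 'decay' the intervention sites are still under the rule and the control sites are still not. An after-to-decay contrast therefore sets exposed against exposed and unexposed against unexposed. If the rule caused a steady excess of missed injuries, that contrast would show no change.

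The protocol itself describes these events as uncommon or extremely rare, so the number of exposed patients limits what can be learned. Half of that exposure falls in 'decay'. If 'decay' is analysed only as a change from 'after', that half adds nothing to the estimate of harm against unexposed experience.

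**Working it through.** **Inputs.** From Sample size: six pairs, 400 patients per hospital per period, variance of the pair difference 0.0066125, detectable difference 0.114, small-sample factor 7/5, and 'decay' the same size as 'after'. Injury prevalence is 0.9% (Background) or 2.0% (phase II results). The protocol gives no expected rate of missed injury, so the harm rates below are assumptions.

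**1. The plan's own figure.** k = (1.96 + 0.84)² × 0.0066125 / 0.114² = 3.9891. Times 7/5 = 5.5847, so 6 pairs. 12 × 400 = 4,800 per period; × 3 = 14,400. All of this reproduces.

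**2. Share of exposure.** Intervention sites: 6 × 400 = 2,400 in 'after' and 2,400 in 'decay'. 2,400 / 4,800 = 50%. Expected injuries at those sites are about 22 to 48 in one year (0.9% to 2.0%) and about 43 to 96 in both.

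**3. Expectation of each contrast.** Let I and C be intervention- and control-site rates, with subscripts B, A and D for the three periods. The harm rate is p0 without the rule and p1 under it, constant over both exposed years.

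- Before-to-after: (I_A − I_B) − (C_A − C_B), expectation p1 − p0.
- After-to-decay: (I_D − I_A) − (C_D − C_A), expectation (p1 − p1) − (p0 − p0) = 0.
- Between arms within 'decay': I_D − C_D, expectation p1 − p0.
- Before-to-pooled: ((I_A + I_D)/2 − I_B) − ((C_A + C_D)/2 − C_B), expectation p1 − p0.

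**4. Precision, for p0 = 0.05% and p1 = 0.20%.** Binomial variances are p0(1 − p0) = 0.00049975 and p1(1 − p1) = 0.001996, with 2,400 patients per arm and period.

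- Before-to-after: √[(0.001996 + 3 × 0.00049975)/2,400] = 0.121%.
- Before-to-pooled: √[(0.001996/2 + 2.5 × 0.00049975)/2,400] = 0.097%.

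The standard error falls by about a fifth, not by half, because the single 'before' year still contributes its full noise.

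**5. Power of the paired t-test.** Two-sided 5%, 5 degrees of freedom, 20,000 simulated trials, binomial counts, no extra between-cluster variance:

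| Contrast | 0.05% to 0.20% | 0.1% to 0.5% |
|---|---|---|
| After-to-decay | 5% | 5% |
| Before-to-after | 16% | 43% |
| Between arms, 'decay' only | 19% | 55% |
| Before-to-pooled | 25% | 62% |

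The 5% for after-to-decay is the size of the test, so that contrast has no power against a constant harm.

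**6. Zero-event limit at intervention sites.** One-sided 95% upper limit = 1 − 0.05^(1/n). For n = 2,400 it is 0.125%; for n = 4,800 it is 0.062%. This describes one arm and ignores clustering.

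**The case against.** A reader might infer that half of the intervention exposure never enters any harm comparison. The document does not support that. The sustainability objective is worded as a comparison of intervention with control sites, with the two periods saying when, and it covers both harms. Control sites receive no implementation strategy, so on that reading 'decay' harms are set against unexposed patients. The basic test is also a between-arm contrast, and Methodological issues describes the 'before' period as the baseline for measuring change. A 'decay' change score could therefore mean decay minus before, in which a constant harm does not cancel. This part of the objection stands. It leaves the reference unclear rather than settled, because the general sentence speaks of the previous period and of baseline together, and the stated purpose of the after/decay comparison is sustainability. On none of these readings is a pooled analysis named.

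It can also be said that a pooled safety contrast is detail for an analysis plan not shown here. But this protocol does choose its period contrasts for these outcomes, so the point is an improvement to a stated choice, not a complaint about a missing detail.

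Two further points stand in part. A steady excess would be present in 'after' too, where before-to-after targets it, and the independent safety board may stop the study at any time. So it does not follow that harm would go unseen or be read as reassuring. The board's monitoring is nevertheless separate from the trial's reported harm comparison.

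Finally, a reader might expect doubled exposure to transform power. A simple comparison of counts with an assumed 4 versus 0.5 events per year gives about 15% on one year and 56% on two. That rests on an eightfold excess and is not the planned test: it ignores pairing, clustering and the 'before' period.

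**Conclusion.** The point holds as a cheap improvement, not as an error that invalidates the plan. The named contrasts for missed injuries and serious adverse outcomes do not combine the two exposed years. The contrast named for 'decay', if run as a change from 'after', cannot show a constant harm. The reference for 'decay' needs to be stated.

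The benefit of pooling is moderate: 16% to 25%, or 43% to 62%, under the two assumed scenarios, and a halved zero-event limit. The power figures assume a harm equal in both years, equal baseline rates in the two arms, 400 patients per site and period, and no extra between-cluster variance. Power stays limited for rare events even with both years. The primary radiography analysis is not affected.

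**What to change.** In the analysis section, for missed injuries and serious adverse outcomes only, add an intervention-versus-control comparison over 'after' and 'decay' combined, with 'before' as baseline, and show each year separately. Keep 'after' versus 'decay' for the radiography rate and length of stay. State whether a 'decay' change score refers to 'before' or to 'after'.

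The cost is about one sentence plus that clarification. The data are already collected in all three periods. The downside is that the pooled safety result is final only after the 'decay' year, so the 'after'-only result should still be reported when it is available.

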#### Performance of the Canadian C-Spine Rule

Performance of the Canadian C-Spine Rule will be evaluated by the following measures.

Accuracy of the rule: The classification performance of the rule for clinically important CSI will be assessed with 95% CIs for sensitivity, specificity, negative predictive value, and positive predictive value. The "criterion interpretation" of the rule, such as positive or negative for CSI, will be made by the investigators based on the status of the patient for the component variables as documented by the physician.

Physician accuracy in interpretation of the rule will be calculated as the simple agreement between the physicians' notation on the requisition – to the investigators' "criterion interpretation" of the rule.

Physician comfort and compliance with use of the rule will be tabulated in a simple descriptive format.

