#### Details of planned interventions

Each ED physician group will be asked to discuss and agree to a policy of ordering cervical spine radiography for alert and stable trauma patients according to the Canadian C-Spine Rule. Minor educational initiatives for the ED physicians will include the distribution of manuscripts, pocket cards, and posters, as well as a single one-hour teaching session to review the evidence and clinical application of the Canadian C-Spine Rule. The ED and Radiology departments will collaborate to institute a process-of-care modification with a mandatory "online" reminder of the Canadian C-Spine Rule at the point of requisition for cervical spine radiography. All cervical spine radiography ordered in the ED will require that the ordering physician complete a special paper or computer-based requisition that includes the Canadian C-Spine Rule algorithm criteria. The physician must "check off" the criteria, or the radiology department will not process the request. The physician may override the rule, and order radiography according to his/her clinical judgment, but will be asked to indicate the reason. Those sites that use paper requisitions will implement a new pad of special cervical spine radiography requisitions. Those sites that order radiography by computer will have an on-screen version of the rule made available by software modification.

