### Outcome measures and data collection

#### Measures of clinical impact

The following will be collected at both the intervention and control sites during all three study periods by dedicated study personnel who will review daily patient logs, ED patient records, radiology reports, and inpatient records.

Cervical spine radiography ordering proportions will be the primary study outcome, such as the proportion of eligible blunt trauma patients referred for plain cervical spine radiography during the initial ED visit. Daily patient census logs will be reviewed to identify potential injury patients, and then ED patient records (e.g., ambulance call reports, nursing notes, and physician notes) will be assessed to determine eligibility. Radiology reports and census lists will be used to determine if cervical spine radiography was performed.

*Number of missed CSI, such as number of clinically important CSI not identified during initial ED visit*. We validated the safety of the Canadian C-Spine Rule with detailed follow-up of patients in phase II. In order to significantly reduce the resources required for phase III, we propose not to specifically follow all patients who do not undergo radiography in the ED. Telephone follow-up of patients is very labor intensive and expensive. Rather, we propose to institute a strategy of surveillance to identify the uncommon occurrence of a fracture missed because no radiography was ordered. The more common missed fracture cases due to mis-reading of the radiograph will be identified through the normal radiology department quality assurance processes. ED patient visit logs at each study site will be monitored for 30 days to identify return visits by patients who do not undergo radiography during their ED visit. In addition, we will review the neurosurgery patient logs at all neurosurgical centers that are the traditional referral sites for the study hospitals. In many cases, the regional neurosurgical centers will be our study hospitals. Application of the same surveillance approach, regardless of phase or intervention group, minimizes the likelihood of bias. We recognize that there is a very small risk of not identifying a missed fracture, but feel that this approach is pragmatic and feasible.

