#### Performance of the Canadian C-Spine Rule

This is a secondary study outcome. The rule will be evaluated during the "after" period at the intervention sites for those cases where physicians have completed the special study requisition and checked off the rule criteria. Rule criteria are:

*Accuracy of the rule, such as sensitivity and specificity for identifying clinically important CSI*. In interpretation of the rule, physician accuracy will be determined by comparing the physicians' notation on the radiography requisition to the "gold standard" interpretation of the rule made by the investigators' steering committee. Attention will be focused on fractures missed or potentially missed by physician misinterpretation.

*Physician comfort and compliance with use of the rule*. On the radiography requisition, physicians will be asked to indicate their comfort in following the rule for that specific patient, using a five-point Likert scale. When physicians choose not to follow the rule, they will be asked to indicate reasons for non-compliance.

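### Physician accuracy in interpreting the rule is reduced to one raw agreement figure, which rises with the rule-positive share of imaged patients and pools the two directions of error

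*Protocol article*

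**What the plan says.** Three parts of the Protocol article define this secondary outcome.

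- **Data analysis, Performance of the Canadian C-Spine Rule.** The statistic is fixed: "Physician accuracy in interpretation of the rule will be calculated as the simple agreement between the physicians' notation on the requisition" and the investigators' criterion interpretation. That interpretation "will be made by the investigators based on the status of the patient for the component variables as documented by the physician".
- **Outcome measures and data collection, Performance of the Canadian C-Spine Rule.** The reference is called a gold standard, namely the "interpretation of the rule made by the investigators' steering committee". The evaluation is made "for those cases where physicians have completed the special study requisition and checked off the rule criteria". The section adds: "Attention will be focused on fractures missed or potentially missed by physician misinterpretation".
- **Details of planned interventions.** The form is tied to an imaging order: "All cervical spine radiography ordered in the ED will require that the ordering physician complete a special paper or computer-based requisition".

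The Specific objectives name the outcome as accuracy in interpretation of the rule.

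**The concern.** There are two separate issues.

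The first is scope. The investigators apply the rule to the components as the physician recorded them. If the physician misjudged a component, the error passes into the criterion as well, and the two readings can still agree. What is tested is whether the physician's conclusion follows from the recorded findings. The gold standard label suggests more than that.

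The second is the statistic. Forms arise where radiography is ordered, so rule-positive patients are likely to be over-represented among them. With one class dominant, raw agreement can be high for a reader who does not discriminate at all. It also counts a rule-positive patient read as negative the same as a rule-negative patient read as positive. The outcome section singles out the first kind of error.

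This matters because the rationale for an implementation study cites phase II problems with accuracy of interpretation as one reason to run phase III. One pooled percentage would not show whether those problems persist in the direction that bears on safety.

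**Working it through.** The article gives no expected agreement, so there is no planned figure to reproduce. The rule-positive shares that feed the check do reproduce.

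**Rule-positive share** = sensitivity × prevalence + (1 − specificity) × (1 − prevalence).
- Phase I (151 injuries in 8,924; sensitivity 100%; specificity 42.5%): 0.0169 + 0.575 × 0.9831 = 58.2%, as stated.
- Phase II without indeterminate cases (8,283 − 845 = 7,438; 162 injuries, 161 identified; specificity 45.1%): 161/7,438 + 0.549 × (1 − 162/7,438) = 0.0216 + 0.5370 = 55.9%, as stated.

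**Ordering rates.**
- Design target (Sample size): 76% − 11.4 points = 64.6%.
- No change: 76%.
- Phase II (Methodological issues): 71.7%.
- The 25% and 50% relative reductions under Potential benefits: 0.75 × 76% = 57% and 0.50 × 76% = 38%.

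**Agreement for a reader who always marks positive** equals the criterion-positive share of forms:
(rule-positive share × fraction of rule-positive patients imaged) ÷ ordering rate, capped at 100%.
The fraction imaged is not given. I assume 100% first and then 85% to 95%. I also assume a completed form for every order.

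| Ordering rate | Fraction of rule-positives imaged | Always-positive agreement |
|---|---|---|
| 64.6% | 100% | 55.9/64.6 = 86.5% to 58.2/64.6 = 90.1% |
| 64.6% | 95% | 82.2% to 85.6% |
| 64.6% | 90% | 77.9% to 81.1% |
| 64.6% | 85% | 73.6% to 76.6% |
| 71.7% | 100% | 78.0% to 81.2% |
| 76% | 100% | 73.6% to 76.6% |
| 57% | 100% (capped) | 98.1% to 100% |
| 38% | capped | 100% |

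Changing one input at a time therefore gives about 74% to 100%. Changing both unfavourably (76% ordered, 85% imaged) gives 62.5% to 65.1%. If ordering is unrelated to the rule, the share is simply 55.9% to 58.2%. Kappa for a constant reader is 0 whenever both criterion classes occur.

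**Pooling of error directions**, at the 64.6% rate with all rule-positives imaged:
- Forms: 6 sites × 400 × 0.646 ≈ 1,550.
- Criterion-positive forms: 2,400 × 0.559 ≈ 1,342, or 2,400 × 0.582 ≈ 1,397. Criterion-negative forms: about 209 or 154.
- Thirty errors in either direction lower agreement by the same 30/1,550 = 1.9 points.
- Split by class, thirty positive-read-as-negative errors are 30/1,342 = 2.2% or 30/1,397 = 2.1% of their class. Thirty reverse errors are 30/209 = 14.4% or 30/154 = 19.5% of theirs.

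The pooled figure cannot tell these two situations apart. The count of thirty is illustrative only.

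**The case against.** The strongest reply is that the outcome is named accuracy in interpretation. Holding the documented components fixed isolates misapplication of the rule, and the article states openly where the criterion comes from. That stands. A reader might infer that the comparison is circular or invalid because assessment errors cannot show. The documents support only a limit of scope and a loose label. Nor do they say that the components come solely from ticks on the form, or show whether the form carries a separate overall mark.

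It can also be said that the article already promises attention to missed or potentially missed fractures. It does, but the analysis section attaches no measure to that promise; the only statistic it fixes is the pooled one.

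A third reply is that the always-positive reader is hypothetical, since physicians must check off criteria and give a reason for an override. That is fair. The figure is a benchmark for reading the result, not a forecast.

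A reader might also object that the result could not be set beside the phase II kappa of 0.63. That argument fails: the phase II value is agreement between two physicians in 142 cases, whereas this measure compares a physician with an investigator criterion in imaged patients.

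Finally, error proportions from requisitions cannot reveal misreadings that led to no radiography. This is correct and remains a limitation after the fix.

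**Conclusion.** The point holds as a weakness in how a secondary outcome is summarised and labelled. The article itself fixes the statistic, so this is not a detail left to an analysis plan. Raw agreement depends on the rule-positive share of imaged patients and merges the error direction of interest with the other.

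The 87% to 90% figure is conditional on every rule-positive patient being imaged and an ordering rate of exactly 64.6%; at that rate it is the maximum. A reader might infer that the trial would report accuracy at that level without any skill behind it. The documents do not support this: they give no expected agreement, they leave ordering to the physician's discretion, and other inputs move the benchmark widely. Unequal weighting of the two classes remains wherever the class shares differ.

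**What to change.** In the analysis section on performance of the rule, replace the single agreement figure with the 2x2 table of physician reading against criterion reading. Report, each with a 95% CI:

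- the proportion of criterion-positive forms read as negative;
- the proportion of criterion-negative forms read as positive.

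Give the observed criterion-positive share beside them as the always-positive benchmark. Kappa is optional, since it is depressed when one class dominates. State that the measure covers interpretation only, and only imaged patients. In the outcome section, replace the gold standard label with criterion interpretation.

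The cost is wording and one table from data already collected. The result may look less favourable than one pooled percentage, and misreadings that led to no radiography remain unseen. I would not rebuild the criterion from ED records: the figure showing the rule's components is not available here, and this would add abstraction work.
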